### Study Procedures

#### Recruitment

A total of 6 recruitment strategies were utilized to ensure enrollment targets were met and a diversity of participants were enrolled to foster a diverse range of sociodemographic characteristics: (1) Web-based banner ads and digital flyers placed through geo-mapping (ie, the ads only displayed in areas where study recruitment was possible) on websites and social media sites that target transgender women, (2) ads placed in print media and via an email blast for transgender women or that transgender women read; (3) street- and venue-based outreach by 2 research assistants (RAs) utilizing a modified semistructured time-space sampling methodology (ie, no sampling frame was created for random selection and sites and times were rotated on a schedule based on known migration tendencies in the community) at locations where young transgender women congregate, such as boutiques, parks, street corners, bars, clubs, hotels, nail and hair shops, and cruising boulevards, (4) study posters placed at collaborating community-based organizations containing details about how to contact an RA for further information regarding the study, (5) in-services at collaborating community-based organizations and other programs on site, and (6) participant referrals. The RAs were trained on appropriate outreach strategies and confidential screening.

#### Enrollment

At the enrollment session, potential participants were screened for eligibility, completed the informed consent process, and were administered a baseline assessment that took approximately 90 min. RAs administered screeners using computer tablets and assessments via audio computer-assisted self-interview (ACASI) to maximize accurate disclosure of high-risk and sensitive behaviors. Questionnaire Development System software was used to implement the ACASI. At the completion of the visit, an RA oriented the participant on how to maintain confidentiality and privacy on mobile devices with respect to the intervention. Participants were shown how to lock their phone, establish and use a pin code to password protect their phone or email account, and were instructed to periodically delete the intervention text messages.

#### Random Assignment

After completing the baseline assessment, participants were assigned to a condition through an urn randomization procedure. The urn randomization procedure provided balance across age (18-24 and 25-34 years), race/ethnicity (Latino/Hispanic and all other race/ethnicities), and HIV care continuum status (linked, nonlinked to HIV care). Participants were randomized into 1 of the 2 conditions: Group A—immediate text message intervention delivery (n=61) or Group B—delayed text message intervention delivery (n=69) whereby participants were delivered the text-messaging intervention after a 90-day delay period. Both groups received the same 90-day text-messaging intervention. The randomized 2-group repeated measures design assessed participants at 3, 6, 12, and 18 months post randomization.

#### Postintervention Opt-In/Opt-Out Retention and Engagement Text Messages

Immediately following the 90-day text-messaging intervention, participants were offered an opportunity to opt in to receive additional weekly text messages at a reduced schedule through their final distal follow-up evaluation. Participants in both study conditions could opt to receive the postintervention messages. Postintervention retention/engagement messages comprised 2 topic areas: (1) linkage/retention support (ie, participant received a message about linking/remaining in HIV care) and (2) ART adherence reminders (ie, participant received a message about the importance of medication adherence); a participant could opt in to any one or both of the topic areas. Each of the 2 topic areas were transmitted once a week for a maximum of 2 weekly messages. Postintervention retention/engagement messages were derived directly from the text messages already available through the Health Resources and Services Administration (HRSA)–funded UCARE4LIFE library. At each follow-up visit, participants were asked if they wanted to opt in/out to receive these additional retention/engagement text messages and were informed that they could stop the additional messages at any time by texting back *stop* to the system.

#### Incentive Schedule

Incentives comprised the following: (1) incentives for admission procedures (US $50 gift card), (2) incentives for completing follow-up assessments (US $50 gift card for completing the 3-month follow-up assessment, a bonus of US $20 for completing the 3-month follow-up assessment within an average of 5 days of the exact 3-month date, a US $50 gift card for completing the 6- and 12-month follow-up assessments, and a US $100 gift card for completing the 18-month follow-up assessment), and (3) a small gift (eg, make-up, earrings; valued at approximately US $2) when an active participant brought a potential participant to the site, and a US $20 gift card if the potential participant was eligible and enrolled (maximum of 3 eligible and enrolled participants per active participant). The total amount a participant could earn for enrolling and participating in the study was US $380.

### Evaluation Procedures

The evaluation plan for *Text Me, Girl!* was 2-fold, with both a cross-site and a local evaluation. Under the sponsorship of the HRSA Special Projects of National Significance (SPNS) Social Media Initiative**,** the Evaluation and Technical Assistance Center (ETAC) at University of California, Los Angeles, was responsible for providing technical assistance and capacity building to the local demonstration sites on clinical and program activities and leading the cross-site evaluation. The cross-site evaluation included both a behavioral and clinical assessment. The clinical assessments were carried out by a medical care provider at one of the collaborating HIV medical care clinics. Once data were collected and abstracted by the HIV medical care provider, FRI submitted the data to ETAC via a Web-based system called the ETAC Social Media Project Portal.

For the local evaluation component, the outcomes were selected based on HRSA priorities and the Los Angeles Enhanced Comprehensive HIV Prevention Plan [17]. *Text Me, Girl!* collected and reported on the required performance measures, including program-specific and required ETAC data at baseline and at follow-up data visits administered at 3 months post enrollment, and approximately 6, 12, and 18 months post enrollment. The project director, research coordinator/evaluator, and RAs were trained in administration of the assessments and on the procedures to be used for data submission to HRSA.

In addition to the local and cross-site assessments, process evaluation and study monitoring were also carried out as part of the overall evaluation of *Text Me, Girl!*. Process evaluation procedures included the following: (1) formative evaluation of the study to update and refine study components that were responsive to the needs of young HIV-positive transgender women, (2) process monitoring of the delivery of the study, and, (3) process evaluation of successful linkage, engagement, and retention among participants. An intervention exposure (IE) question was administered as part of the reporting protocol. Using the study mobile phone, an RA sent a monthly IE text message to each participant on a Wednesday afternoon between 3:00 pm and 7:00 pm. The IE text message was as follows: “In the past month, how many of the text messages did you read? Please text back one of the following: 1) none, 2) some but less than half, 3) about half, 4) a lot but not all, or 5) all.”

Outcome data were generated through 2 mechanisms: (1) assessments performed onsite at baseline and at 3, 6, 12, and 18 months post baseline and (2) electronic medical record (EMR)/electronic health record (EHR) data abstraction. In each case, data were imported from delimited text format (ie, .csv, the native format for the cloud-based data storage, scanned paper assessments, and extracted EMR/EHR data) into Stata v13SE (StataCorp).

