**Figure 1 figure1:**
[figure not shown]
*Text Me, Girl!* study design. f/u: follow-up; HRSA: Health Resources and Services Administration; mo: month.

Only the messages related to the HIV care continuum were modified: (1) HIV positivity/physical and emotional health, (2) linkage/retention in HIV care, and (3) ART medication adherence/viral load suppression. The text message library was tailored specifically to the needs of young transgender women living with HIV in terms of verbiage and content. The text message library was personalized in that participants could customize their 10-hour delivery timeframe, that is, intervention time period, and could personalize their delivery platform to their mobile phone or an email inbox. Several iterations occurred; the first level of modifications was made with 4 young adult transgender service providers who were given the original text-message library to adapt for young adult transgender women living with HIV. Following several revisions, the library was brought before the transspecific Community Advisory Board for the second level of modifications. The Community Advisory Board is multicultural and comprised both transgender women living with HIV and HIV-negative transgender women, program consumers, gatekeepers and stakeholders, service providers from local community-based organizations that provide services to transgender women, and members of local community planning and advocacy groups (eg, LAC Commission on HIV, Transgender Service Providers Network, and Transgender Task Force). The Community Advisory Board members reviewed and discussed every message in detail. Following the adaptation into a culturally responsive text-message library for young adult transgender women living with HIV, the research team reviewed each message and, if necessary, made minor modifications to ensure that each message had a theoretical foundation.

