### Sample

The study inclusion criteria were as follows: gender identity as a woman, assigned a biological sex of male at birth, aged between 18 and 34 years, confirmed HIV-positive serostatus, ability to receive daily text messages on either a personal mobile phone or via an email account, tested HIV positive for the first time within the last 12 months or had not had an HIV care visit in the previous 6 months or had a viral load of ≥200 copies/mL on her last lab test result or not currently prescribed ART medication or was currently prescribed ART medication but did not rate her ability to take all her medications as excellent, willing and able to provide informed consent, and willing and able to comply with study requirements. Individuals were excluded if they did not meet all the eligibility criteria.

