### Measures

All primary outcomes came directly from the US Health and Human Services (HHS) Common HIV Indicators for the HRSA/SPNS project (FOA HRSA-15-029). Utilization of these collection procedures provided data that could be compared with other clinical services and programs serving high-risk populations and populations that are underrepresented in HIV care. As the ETAC cross-site evaluation procedures and measures are described in detail elsewhere [48], only the local evaluation measures are described below.

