### Statistical Analyses

Table 2 provides all evaluation outcomes and their chosen measurement models. Power calculations are based on assumptions of alpha=.05 (2-tailed tests), a sample size of 130 HIV-positive young transgender women, and a power standard of 0.80. It was calculated that logistic regression analyses of primary outcomes would be able to find a minimum detectable odds ratio of 2.98 for linkage/uptake of ART and achievement of an undetectable viral load (the primary outcomes of interest).

**Table 2 table2:** Study outcomes and measurement models.

Primary outcome	Measurement model
Linkage to HIV primary care (self-report and EMR^a^/EHR^b^ abstraction)	0= Participant did not attend HIV medical visit within 3 months of enrollment; 1= Participant attended within the first 3 months
Prescribed ART^c^ medication (self-report and EMR/EHR abstraction)	0=Participant is not prescribed HIV medication; 1=Participant is prescribed HIV medication
Retention in HIV primary care (self-report and EMR/EHR abstraction)	0=Participant did not attend a second HIV care appointment after the initial 3 months; 1=Participant attended an additional HIV primary care visit after the initial 3 months
ART adherence (self-report)	Ordinal scale (Likert)
Viral load monitoring (self-report and EMR/EHR abstraction)	Binary (0=>200 copies/mL, 1=<200 copies/mL)

^a^EMR: electronic medical report.

^b^EHR: electronic health report.

^c^ART: antiretroviral therapy.

All regression analyses assess assumptions of normality and model fit. In addition to the primary outcomes listed in Table 2, participants were assessed for changes in their HIV-related self-efficacy from baseline to follow-up evaluations. The HIV-ASES scale was used to assess HIV self-efficacy, producing continuous values suitable for ordinary least squares (OLS) regression. In addition, if during implementation, a sufficient number of participants opted in to receive one or more of the postintervention retention/engagement text messages available through final distal follow-up evaluation, additional analyses were carried out to estimate the observed effect(s) of receiving these postintervention text messages.

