All calculations of detectable effects for primary outcomes were based on expected cultural/demographic subgroup analyses premised on known social determinants of risk (eg, racial/ethnic identity, language and health insurance) and are displayed in Table 2. Secondary analyses related to HIV self-efficacy were analyzed using OLS regression and should produce detectable effects at *f*^2^=0.067. Given these values, detectable effects of all analyses should, if benchmarked, fall in the *small to moderate* to *moderate* ranges. Given an expected follow-up rate of at least 85% (111/130) at each time point, associations between primary outcomes and optional postintervention retention/engagement messages should produce minimum detectable effects exhibiting a 3% (repeated measures survival analysis testing time-based dichotomous outcomes, eg, linkage) to 18% (OLS regression for secondary analyses, eg, HIV-related self-efficacy scores) increase in detectable effect size (ie, outcomes will be more difficult to detect), resultant from participant attrition.

Primary outcome analyses comprised bivariate contrasts of outcomes over time (ie, HIV care continuum outcomes at baseline and each follow-up, with differences tested via *t* test and chi-square analyses) and multivariate analyses of these same outcomes regressed on random study arm assignment, self-reported exposure to theory-based text messages, and time. Observations were nested within participants, and sociodemographic controls were tested for inclusion during sensitivity testing of the models. Secondary outcomes included sexual risk behaviors, substance use, self-efficacy, and changes in gender identity over time.

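### The only exposure question described is sent and answered by text, although delivery may be by email, so the exposure term in the primary models is at risk of non-random missingness

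*Protocol article*

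**What the plan says.** Sample, in the protocol article, accepts "ability to receive daily text messages on either a personal mobile phone or via an email account", so an email account is enough for entry. Study Design (text after Figure 1) adds that participants "could personalize their delivery platform to their mobile phone or an email inbox".

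Evaluation Procedures describes one exposure item: "Using the study mobile phone, an RA sent a monthly IE text message to each participant on a Wednesday afternoon". The item asks how many of the messages were read in the past month, and the reply goes back the same way: "Please text back one of the following: 1) none, 2) some but less than half, 3) about half, 4) a lot but not all, or" a fifth option for all of them. No email version of the question is described.

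Statistical Analyses states that the primary outcomes are "regressed on random study arm assignment, self-reported exposure to theory-based text messages, and time", with observations nested within participants. Exposure is thus a regressor in the primary multivariate models and not only a process measure.

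Measures limits what can be seen here: "As the ETAC cross-site evaluation procedures and measures are described in detail elsewhere [48], only the local evaluation measures are described below".

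**The concern.** The intervention has two channels and the exposure question has one. A woman who takes part by email and has no phone that handles texts can neither receive the question nor answer it.

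A second difficulty does not depend on email. To be recorded as having read *none* of the messages, a woman must open a text and reply to it. Women who ignore texts are the least likely to do so. Non-reply therefore plausibly depends on the very quantity being asked about, and engagement plausibly relates to linkage, retention and adherence.

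Two things are at stake. A regression that requires an exposure value omits observations without one, and a woman who never replies can leave the primary model altogether although she was randomised and her outcome is known. The exposure coefficient, and any dose-response statement built on it, would then rest on a group selected for engagement.

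**Working it through.** The point rests on no figure in the plan, so it is checked by setting the sections side by side. The arithmetic at step 4 is context only.

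1. **Who can be reached.** Entry: phone or email (Sample). Delivery: phone or email (Study Design). Exposure question: text out, text back (Evaluation Procedures). The third is narrower than the first two. Missingness is certain only for women without a text-capable phone; for other email users it is possible.

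2. **Who replies.** All five answers, including *none*, require a text reply. The probability of a recorded value therefore probably falls as exposure falls, which is missingness related to the missing value.

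3. **What this does to the model.** At 3 months Group B is still at the end of its 90-day delay (Random Assignment), so its exposure to the 270 theory-based messages is zero by design and needs no reply. There are two cases.
   - If a reply is required of everyone, women are lost from both arms.
   - If Group B is set to zero and a reply is required only in Group A, women are lost from Group A alone. Let a share *m* of Group A not reply, *p* be Group A's true success rate and *q* the rate among non-repliers. The rate among those kept is (*p* − *mq*)/(1 − *m*), which exceeds *p* by *m*(*p* − *q*)/(1 − *m*). This is positive whenever non-repliers do worse (*q* < *p*). It describes who enters the model, before any exposure adjustment.

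4. **Precision, as illustration.** Inputs from the article: "alpha=.05 (2-tailed tests), a sample size of 130 HIV-positive young transgender women, and a power standard of 0.80", and arms of 61 and 69. The stated minimum detectable odds ratio is 2.98, but no reference rate is given. A two-proportion calculation with 69 and 61 gives 2.96 at a reference rate of 20%, 2.75 at 30%, 2.81 at 50% and 3.07 at 60%. So 2.98 is attainable but cannot be verified. Assume a reference rate *p*₀ of 50%, that women without an exposure value leave the model, and that the loss is proportional in both arms. Remaining sample = 130 × (1 − *m*). The odds ratio OR is solved for power 0.80, with *p*₁ = OR·odds₀/(1 + OR·odds₀) and odds₀ = *p*₀/(1 − *p*₀).

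| Share missing (assumed) | Women left | Detectable odds ratio |
|---|---|---|
| 0% | 130 | 2.81 |
| 10% | 117 | 2.99 |
| 20% | 104 | 3.22 |
| 30% | 91 | 3.53 |
| 40% | 78 | 3.98 |

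This treats one time point with independent observations; the planned nested model would give other values. The 85% (111/130) follow-up rate in Statistical Analyses concerns follow-up time points, not replies to this question, so it does not settle which row applies.

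**The case against.** **Email recipients may own phones.** A reader might infer that exposure is missing for everyone who chose email. The article does not support that: it says the question went to each participant, and choosing email does not mean having no phone. Nothing shows that a woman without a text-capable phone was enrolled. This stands, and it limits the point to a risk.

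**Other exposure measures may exist.** The cross-site measures are described elsewhere, process monitoring of delivery is mentioned, and Statistical Analyses does not name the item behind its exposure term. This also stands: the monthly text is the only measure described, and probably but not certainly the one used.

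**Group B and the later opt-in messages.** A reader might infer that Group B was asked during its delay about messages it had not had, or that later answers mix the 270 messages with the weekly opt-in ones. Both depend on when the monthly question started and stopped, which the article does not say. A condensed article may leave that out.

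**No share can be put on the loss.** A reader might try. Assume 5% to 20% without a usable phone and 30% non-reply among the rest: 0.05 + 0.95 × 0.30 = 0.335 and 0.20 + 0.80 × 0.30 = 0.44. But the item repeats monthly. If a woman lacks a value only when she misses all three prompts, and misses are independent, 0.30³ = 0.027, giving 0.05 + 0.95 × 0.027 = 0.076 and 0.20 + 0.80 × 0.027 = 0.222. Real non-reply is correlated, so the result would lie between. None of these inputs has an anchor in the article, and its Introduction reports over 90% internet and mobile phone use at ages 12 to 29. No such figure should be quoted as the size of the problem.

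**Missing-data rules belong in the analysis plan, and the bivariate contrasts carry no exposure term.** The first is fair; the absence of a rule is not the complaint. The second is true, but those contrasts are described as outcomes over time, while arm appears in the multivariate models together with exposure. The objection therefore does not remove the problem.

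**Conclusion.** The point holds as a risk built into the stated design. Entry and delivery allow email alone, the described exposure item works by text alone, and self-reported exposure sits beside arm in the primary multivariate models. Missing replies can therefore drop randomised women and bias the exposure term, probably in relation to engagement.

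The number of women affected is not stated and cannot be derived. The conclusion assumes that the monthly item supplies the exposure regressor, that non-reply is commoner among less engaged women, and that the model needs an exposure value for an observation to count. The table shows only how precision would suffer over a range of losses; it does not estimate the loss. Results places the primary analyses after follow-up ends on August 31, 2019, so the models can still be changed.

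**What to change.** **Primary analysis.** Estimate the arm effect in all randomised women in a model without the exposure term, so that no woman is lost for not replying.

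**Secondary analysis of exposure.**
- Set Group B's exposure to the 270 theory-based messages to zero by design during the 90-day delay.
- Use only replies that refer to each woman's own 90-day intervention period.
- Add the automated system's delivery record, phone or email, as a channel-neutral measure. That this record was retained is an assumption to confirm.
- Treat non-reply as missing rather than as *none*, with a sensitivity analysis that scores it as *none*.
- Report reply rates by arm and delivery channel, and state how the question reached women who used email.

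**Cost.** A change of model specification, one extract from the delivery system and a short table of reply rates; no new contact with participants. A new recall question is not worth adding, since delivery ended on November 30, 2018. The downside is that the record shows delivery rather than reading and may vary little within an arm, so the text-back item stays as supportive evidence.
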